## Abstract

**Background:**

Blood donors are at risk for reduced iron stores, because of which donor iron monitoring received increased attention in the last decade. Despite the importance for donor health, international consensus on an appropriate policy for iron monitoring is lacking. Therefore, we conduct a trial to evaluate to what extent ferritin-guided donation intervals are effective in increasing haemoglobin and ferritin levels, decreasing low-haemoglobin deferral, increasing donor return and improving the health of whole blood donors in the Netherlands.

**Methods:**

Sanquin Blood Bank is implementing ferritin-guided donation intervals to prevent donors from increasing iron loss at repeated donations. Using a stepped wedge cluster randomised trial approach, the design involves a random crossover of 29 clusters of blood collection centres from the existing policy without ferritin measurements to a ferritin-guided donation interval policy. This new policy includes ferritin measurements for all new donors and at every 5th whole blood donation, extending donation intervals to 6 months if ferritin is 15–≤ 30 ng/mL and to 12 months if ferritin is < 15 ng/mL. We measure ferritin levels of whole blood donors from stored plasma samples and collect haemoglobin levels and information on low-haemoglobin deferral and donor return from the donor database before, during and after the implementation period. We measure donor health during and after the implementation period using questionnaires, assessing physical and mental wellbeing and iron deficiency- and donation-related symptoms. We use multilevel analyses to investigate differences in ferritin and haemoglobin levels, low-haemoglobin deferral rates, donor return and donor health from whole blood donors, between blood collection centres that have versus those that have not yet implemented the ferritin-guided donation interval policy.

**Discussion:**

This stepped wedge cluster randomised trial will provide insight into the effectiveness of ferritin-guided donation intervals in lowering iron deficiency, decreasing donor deferrals due to low haemoglobin and improving donor health. We will evaluate a policy that is implemented nationwide in a real-life setting. Our study is therefore not limited to a small experimental setting and the results will guide policymakers seeking an appropriate policy for iron monitoring.

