### Research objectives

The FIND’EM study evaluates, by means of a nationwide stepped wedge cluster randomised trial, the effects of the ferritin-guided donation interval policy for whole blood donors on (1) Hb and ferritin levels, (2) low-Hb deferral, (3) donor return rates and (4) donor health (i.e. physical and mental wellbeing and iron deficiency- and donation-related symptoms) [14]. We anticipate that the implementation of routine ferritin measurement in whole blood donors and extension of the donation interval in case of low ferritin levels will result in a decrease in low-Hb deferral rates and increase in ferritin and Hb levels, donor health and return rates.

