### Intervention: ferritin-guided donation intervals

The ‘intervention’ includes ferritin-guided donation intervals with ferritin measurements in whole blood donors at pre-donation screening and every 5th donation, in addition to the standard Hb measurement as described as the control condition. Ferritin level cut-offs are based on the definitions for iron deficiency (< 15 ng/mL) and reduced iron level (≤ 30 ng/mL) by Alvarez-Ossorio et al. [12]. With respect to the duration of donation intervals, it is acknowledged that iron-deficient donors may need tailored donation intervals but knowledge on optimal recovery times for iron-deficient donors is lacking. Our deferral period is based on the study by Schotten et al. in which recovery of ferritin levels in new and repeat male donors was suggested to require donation intervals of 180 days [5]. If ferritin during the pre-donation screening is higher than 30 ng/mL, the donor is allowed to donate following regular donation schedules. If ferritin is ≤ 30 ng/mL but ≥ 15 ng/mL, the donor is allowed to donate during the next visit to the blood collection centre, but ferritin will be measured again from the blood sample taken during their first whole blood donation. If ferritin during pre-donation screening is < 15 ng/mL, the donor is not allowed to donate for 12 months. After 12 months, the donor is allowed to donate but ferritin is measured again from the blood sample taken during their first whole blood donation. If the donor experiences complaints that can be associated with a low ferritin level, the new donor is advised to visit his/her general practitioner (Fig. 3).

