### Data collection

Pseudonymized data on age, sex, Hb levels and deferrals will be extracted from the donor database (eProgesa software application; MAK-SYSTEM) for all new and repeat whole blood donors who visit a fixed blood collection centre during a pre-selected week at one of the three measurement time points and gave consent for their information and left-over material to be used for research purposes. Furthermore, we will calculate donor return rates as the percentage of donors with a donation attempt within 6 months after the next allowed donation date. We will use stored plasma samples of new donors and repeat donors who made a donation attempt at one of the fixed blood collection centres during one of the pre-selected measurement time points to determine ferritin levels in intervention and control groups. Ferritin will be measured on the Architect i2000sr (Abbott Diagnostics) from donation samples collected in K3EDTA tubes (Greiner) and stored at − 30 °C. After storage, ferritin levels may be lower than those in fresh samples [16]. Within the FIND’EM study, we will compare ferritin levels of donors donating at centres where the ferritin-guided donation interval policy was implemented to ferritin levels of donors donating at centres where the policy was not implemented yet. For both groups, we will use samples that were stored for the same time period. Therefore, we expect similar decreases of ferritin levels as a result of storage in both groups, still allowing this comparison. For the validation of ferritin levels from stored samples of donors participating in the FIND’EM study, we will compare ferritin levels from stored samples with ferritin levels measured in fresh samples as part of the ferritin-guided donation interval policy.

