### Data analyses

Descriptive statistics will be provided for the donor population at baseline, mid-implementation and after full implementation. Linear mixed models (i.e., multilevel analysis) will be used to investigate differences in Hb and ferritin levels, low-Hb deferral, donor return rates and donor health between intervention and control groups using data collected at baseline, mid-implementation and after implementation. Two-level models with donors nested within blood collection clusters will be fitted, with a random intercept for cluster to adjust for the correlation between measurements of donors within the same cluster. All models include a binary variable indicating whether the observation was done before or after the start of the intervention and will be adjusted for the time point of implementation of the policy (fixed variable, time in months since the start of implementation period). Because of the nature of our outcome measures and because we include a new sample of donors at every measurement time point, we do not expect robust methods to be appropriate for sensitivity analyses. To investigate how the impact of ferritin-guided donation intervals develops over time, the latter will also be included as an effect modifier [14]. An intention-to-treat approach will be used and stratified analyses will be performed to investigate differences in the effectiveness of ferritin-guided donation intervals for male and female donors.

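### The abstract promises a finding on iron deficiency, but the only ferritin outcome named is the level across all attending donors; no outcome uses the plan's own 15 or 30 ng/mL thresholds

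*Protocol article*

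**What the plan says.** The Discussion paragraph of the abstract says the trial will "provide insight into the effectiveness of ferritin-guided donation intervals in lowering iron deficiency". The section on the intervention takes its cut-offs from the "definitions for iron deficiency (< 15 ng/mL) and reduced iron level (≤ 30 ng/mL"), so the article has a working definition of iron deficiency. Under the policy, repeat donors above 30 ng/mL keep normal intervals. Those from 15 to 30 are deferred for 6 months and those below 15 for 12 months.

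Wherever the ferritin outcome is stated, it is the level:
- Research objectives: the policy "will result in a decrease in low-Hb deferral rates and increase in ferritin and Hb levels, donor health and return rates".
- Data collection: the measured population is everyone attending, whatever their ferritin: "We will use stored plasma samples of new donors and repeat donors who made a donation attempt" in the selected weeks.
- Sample size calculations: a mean difference of 4 ng/mL with SD 54 ng/mL.
- Data analyses: linear mixed models for "differences in Hb and ferritin levels, low-Hb deferral, donor return rates and donor health between intervention and control groups".

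The only planned stratification is by sex: "stratified analyses will be performed to investigate differences in the effectiveness of ferritin-guided donation intervals for male and female donors".

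**The concern.** The promised conclusion and the named outcome are different quantities. Iron deficiency is a state below a threshold, and the policy acts on the lower part of the ferritin distribution. The level averages over all attending donors, including those above 30 ng/mL whose intervals do not change. Two policies with the same effect on the mean can therefore differ in their effect on deficiency.

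At stake is whether a statement about iron deficiency, offered as guidance to policymakers, will rest on a pre-named outcome. If it does not, either the statement is inferred from a shift in the mean, or a threshold summary is chosen after the ferritin results are known.

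**Working it through.** **Reproducing the plan's figure.** Inputs from Sample size calculations: difference 4, SD 54, two-sided 5%, power 80%.

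n per arm = 2 × (1.960 + 0.842)² × 54² / 4² ≈ 2,861, so 5,722 in total against the stated 5,720. This confirms that the trial is sized on mean ferritin across all donors, with a planned effect of 4/54 = 0.074 SD.

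**A bound that needs no distribution.** Let p be the share of donors below 15 ng/mL (not given). Each such donor needs a gain of less than 15 to reach 15, so lifting all of them just to 15 moves the mean by less than 15 × p:
- p = 5%: under 0.75 ng/mL
- p = 10%: under 1.5 ng/mL
- p = 20%: under 3.0 ng/mL

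15 × p is below 4 whenever p < 4/15 = 26.7%. This is the least shift that would remove deficiency. The true shift is larger if donors rise beyond 15.

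**Illustration under an assumed distribution.** The article gives no distribution. Assume log-normal ferritin with SD 54 and mean M from 40 to 80, so σ² = ln(1 + (54/M)²). Suppose every donor at or below 30 gains 50% and nobody else changes.
- Shift in the mean = 0.5 × share ≤ 30 × mean ferritin among those donors. For M = 50: 0.5 × 0.444 × 17.3 = 3.84.
- Total N on the mean uses the formula above, with the SD after the gain (52.0 to 52.8).
- n per arm for the share below 15 = [1.960√(2p̄q̄) + 0.842√(p₁q₁ + p₂q₂)]² / (p₁ − p₂)².

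Clustering is ignored, as in the stated 5,720.

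| Assumed mean | Share ≤ 30 | Share < 15, before → after | Shift in mean (ng/mL) | Total N, mean | Total N, share < 15 | Ratio |
|---|---|---|---|---|---|---|
| 40 | 58.9% | 32.4% → 19.6% | 4.3 | 4,732 | 368 | 12.9 |
| 50 | 44.4% | 17.6% → 8.2% | 3.8 | 5,754 | 398 | 14.5 |
| 60 | 30.3% | 7.8% → 2.6% | 3.0 | 9,600 | 570 | 16.8 |
| 70 | 18.5% | 2.8% → 0.6% | 2.0 | 21,760 | 1,102 | 19.7 |
| 80 | 9.8% | 0.8% → 0.1% | 1.1 | 68,430 | 3,070 | 22.3 |

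**Sensitivity to the assumed gain.** With a 25% gain the ratio runs from 19,446/1,164 = 16.7 to 278,992/6,348 = 43.9. With a doubling it is about 8 throughout (1,132/142 = 8.0 to 16,564/2,186 = 7.6). The direction is stable, but the size is not.

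**The case against.** **Lowering iron deficiency is not a listed objective.** The phrase occurs once, in the abstract, as something the trial will give insight into. The stated aim, the objectives and the analysis agree with one another on levels, deferral, return and health. This stands, so one sentence is out of line with an otherwise consistent plan.

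**A reader might infer that the trial cannot show an effect on deficiency.** The documents do not support that. Individual ferritin values will be measured, so the proportions can be computed. A condensed article may also leave scale and summaries to a fuller document. What remains is that the article names the ferritin quantity and the target difference on the level, and then states a conclusion about something else.

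**A reader might infer that the mean hardly registers change in the donors the policy acts on.** That depends on unstated inputs. At assumed means of 40 and 50, a 50% gain moves the mean by about the planned 4 ng/mL, and the required N is close to 5,720. The article also reports a mean increase of 4 ng/mL in the first clusters and more low-ferritin donors than anticipated, so a very small shift should not be presumed. A log scale would be more sensitive (total N 572 to 7,476 in the same scenarios), though it still would not estimate deficiency.

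**A reader might infer that a 4 ng/mL rise could come wholly from donors above 30.** Arithmetically this needs 4/(1 − 0.589) = 9.7 to 4/(1 − 0.098) = 4.4 ng/mL per such donor. But the policy leaves those donors' intervals alone, and the article suggests no mechanism for such an effect. Samples are also fresh cross-sections, so a donor who recovered under the policy may now sit above 30.

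**A proportion among attendees has its own weakness.** Donors found low are deferred for 6 or 12 months and are under-represented in a measurement week. The share below 15 can fall without any donor's iron improving. This stands. It affects the mean too, but the proportion more directly.

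**Conclusion.** The point holds as a mismatch between a stated conclusion and the named outcomes. The abstract refers to lowering iron deficiency and the article defines that state, but no outcome uses the definition. The level answers the question only indirectly. Deficiency could in principle be removed with a mean shift smaller than the 4 ng/mL the trial is sized for, at any prevalence under about 27%; this bound needs no distributional assumption.

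The gain in efficiency from a proportion is real in every scenario run, at roughly 13 to 22 times fewer donors with a 50% gain. That figure assumes a log-normal shape, SD 54 as the SD of the level, means of 40 to 80, gains confined to donors at or below 30, and a similar clustering effect on both outcomes. The article does not say whether 54 is the SD of the level or of the change. The figures support adding a threshold outcome. They do not show that the planned analysis of levels is uninformative, nor that the proportion alone should carry the conclusion uncritically.

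**What to change.** Add two named ferritin outcomes alongside the level: the proportions of repeat donors with ferritin below 15 ng/mL and at or below 30 ng/mL. Report them by sex and analyse them with a logistic mixed model that keeps the planned random intercept for cluster and adjustment for time. Rest any statement about iron deficiency on these outcomes. If they are not added, reword the abstract so that it speaks of ferritin levels.

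The cost is wording and analysis only, because the values come from the same stored samples. Trial status has those measurements scheduled for 2020, so the outcomes should be named before the results are seen.

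Two caveats belong in the text:
- **Storage loss.** Fixed thresholds are sensitive to lower readings in stored plasma. The stored-versus-fresh comparison already planned under Data collection should inform how the thresholds are applied.
- **Deferred donors.** They are under-represented in the measurement weeks, so a lower proportion among attendees may partly reflect their absence and must be interpreted accordingly.

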**Trial registration:**

The Dutch trial registry NTR6738. Registered on 29 September 2017. Retrospectively registered.

## Introduction

As a result of one donation, whole blood donors lose 8% (men) to 81% (menstruating women) of their total iron stores [1–3]. High donation frequency increases the risk for depleted iron stores through the haemoglobin (Hb)-bound iron loss and subsequent increased erythropoiesis [4, 5]. Depletion of iron stores, iron-deficient erythropoiesis and iron-deficiency anaemia may not only negatively influence donor health [6], but may also lead to a higher risk of low-Hb deferral [7], which is demotivating for a blood donor and costly for blood banks [8]. Most blood banks monitor donors’ Hb levels and defer donors with Hb levels below a certain threshold, aiming to avoid anaemia, minimise low-Hb deferral and ensure sufficient Hb content for transfusion [9]. However, these Hb levels do not reflect the donors’ iron status [5, 10] and the World Health Organization advises the monitoring of serum ferritin to detect iron deficiency [11].

Iron deficiency in whole blood donors can be prevented by extending donation intervals or providing iron supplements [5, 9, 12]. Extending donation intervals might be the preferred method in light of possible gastrointestinal disturbances as a result of iron supplementation, poor compliance or negative perceptions of taking iron tablets [12]. Previous studies have shown that prolonged donation intervals are associated with lower risk of low-Hb deferrals [8, 13]. Additionally, the results from the randomised-controlled INTERVAL trial have shown that donating at 8-week intervals for men and 12-week intervals for women lead to significantly lower Hb and ferritin concentrations than those observed in longer donation interval groups (i.e. 12-week intervals and 16-week intervals for men and women, respectively) [8].

Sanquin Blood Bank, solely responsible for the collection and distribution of blood products in The Netherlands, decided to implement a new policy for whole blood donors based on ferritin-guided donation intervals. This policy includes the measurement of ferritin levels, in addition to the regular Hb measurement, prior to the first donation of each new donor and after every fifth whole blood donation. If ferritin levels are low, donation intervals are extended to 6 or 12 months. In order to enable a scientific and methodologically sound evaluation of its effectiveness, limit the anticipated (temporary) impact on donor availability and to provide logistical benefits to the implementation of the new policy, Sanquin Research advised the Blood Bank to implement the ferritin-guided donation interval policy following a stepped wedge approach, involving random cross-over of blood collection centres from the existing policy without ferritin measurement to the policy including ferritin-guided donation intervals.

### Research objectives

The FIND’EM study evaluates, by means of a nationwide stepped wedge cluster randomised trial, the effects of the ferritin-guided donation interval policy for whole blood donors on (1) Hb and ferritin levels, (2) low-Hb deferral, (3) donor return rates and (4) donor health (i.e. physical and mental wellbeing and iron deficiency- and donation-related symptoms) [14]. We anticipate that the implementation of routine ferritin measurement in whole blood donors and extension of the donation interval in case of low ferritin levels will result in a decrease in low-Hb deferral rates and increase in ferritin and Hb levels, donor health and return rates.

## Method

### Setting

The Sanquin Blood Bank is the only organisation authorised to collect, prepare and distribute blood products, in the Netherlands. All donations are voluntary and non-remunerated. Sanquin consists of 50 fixed blood collection centres, organised into blood collection clusters, 29 in total, distributed over four different topographic regions. Each cluster consists of one to three fixed blood collection centres, some also including mobile collection centres. New donors have to undergo an eligibility test before their first blood donation. This pre-donation screening includes checking of health conditions and risk behaviours by means of a donor health questionnaire and interview, blood pressure and Hb testing and blood sampling for blood typing and infectious disease testing. When eligible, men can subsequently donate a maximum of 5 times/year (minimum donation interval of 56 days) and women a maximum of 3 times/year (minimum donation interval of 120 days).

### Study design

The FIND’EM study is a stepped wedge cluster randomised trial involving whole blood donors from all 50 fixed blood collection centres in the Netherlands. The stepped wedge cluster randomised design is increasingly being used in the evaluation of ‘service delivery type interventions’, which are bounded by logistical or policy constraints. A stepped wedge design is a one-way crossover trial in which several allocation groups start at different time points with the implementation of the new policy [14]. For FIND’EM, this involves random and sequential crossover of clusters from the current policy without ferritin measurements to the policy including ferritin-guided donation intervals, until all clusters are exposed to this new policy (Fig. 1). The numbers 1 to 29 have been randomly assigned to one of the 29 blood collection clusters. Allowing only a maximum of two clusters of a similar topographic region to each implementation step, the two clusters with the lowest numbers from each region were allocated to step 1, the clusters with the third and fourth lowest numbers from each region were allocated to step 2, the clusters with the fifth and sixth lowest numbers from each region were allocated to step 3 and the remaining clusters were allocated to step 4. The allocation was not concealed and the planned timing of crossover of all blood collection clusters was revealed before the start of the implementation period. In November 2017, Sanquin started with implementing ferritin-guided donation intervals in eight clusters of blood collection centres (28% of all blood collection centres). The next three implementation steps were planned for May 2018, October 2018 and February 2019. The number of repeat whole blood donors with low ferritin levels appeared to be higher than anticipated. Therefore, to ensure sufficient blood supply in The Netherlands, further implementation had to be delayed and executed in smaller steps. The second step of implementation thus included four clusters of collection centres from different topographic regions (step 2a), instead of the planned eight clusters, and was scheduled for May 2018. The remaining clusters of step two implemented ferritin-guided donation intervals in October 2018 (step 2b). The third step was again split into two implementation waves, in which four clusters implemented the policy in March 2019 (step 3a) and three additional clusters of step 3 started in October 2019 (step 3b). Due to logistical reasons, one cluster randomised to step 3 was not able to implement the ferritin-guided donation intervals in October 2019. The fourth and final step included the remaining six clusters of collection centres and was executed in November 2019 (Fig. 1). On average, a total of 1275 whole blood donations are done at collection centres of each implementation step per week. Effectively, this stepwise strategy results in a gradual increase of the intervention group and a simultaneously decreasing control group. This implementation strategy and the ferritin-guided donation interval policy itself was approved by Sanquin’s Board of Directors after review and approval by Sanquin’s Medical and Ethical Advisory Boards. Additionally, Sanquin’s Ethical Advisory Board has approved the FIND’EM protocol for additional questionnaires and ferritin measurements. As part of standard practice, blood donors are asked for consent for their unusable remainder of the donation to be used for medical scientific research. Consent for the use of this material was included in the ethical approval for the current study. All research activities commenced after ethical approval was obtained. All participating donors who filled in a questionnaire provided additional written informed consent. As the FIND’EM study is a minimal risk study, a data monitoring committee is not needed.
